#### Management and administration of medication

The CBM oil (CogniCann; MGC Pharmaceuticals Ltd., Perth, Australia) will be provided in a sealed 10-ml glass spray bottle which contains a mix of THC and CBD in a 3:2 ratio (25 mg/ml THC; 17 mg/ml CBD) in a medium-chain triglycerides oil base. Each press of the vial will accurately dispense 100 μl of oil that contains 2.5 mg of THC. A total of 50 mg/day of THC and 34 mg/day of CBD can be administered for 4–5 days from one 10-ml glass spray bottle. CogniCann can be stored at room temperature (below 25 °C) for a total of 4 weeks. A certificate of analysis will be provided for each batch upon delivery.

The placebo will be administered in the same 10-ml glass spray bottle and collected following the procedures describe above. The placebo will comprise a terpene-based oil that contains esters that mimic the smell and taste of CBM.

The bottles of medication will be provided to the residential aged-care facilities by the affiliated pharmacist. The bottles will be delivered every week and collected again after 7 days of use (even if they are half-full) and returned to the pharmacy, where staff can determine how much was used (or left) and then dispose of the bottles to meet Therapeutic Goods Administration (TGA) requirements. At the start of the titration phase, one bottle will be administered for each participant (because the lower dose of 2.5 mg of THC allows for each bottle to hold 2–3 weeks of the medication). As participants begin to reach a higher dose (titration phase; *see* Table 1), two bottles will be provided on a weekly basis so that each participant will have sufficient medication to last for 7 days.

### Data collection

The aged-care staff, resident participants with dementia, and nominated next of kin will complete a total of four outcome measures on seven occasions throughout the study. The questionnaires take approximately 20 min to complete and will be completed three times during the first treatment arm (baseline [day 0], after maximum tolerated dose has been reached [day 24], and the end of the treatment cycle [day 42]), three times during the second treatment arm (baseline [day 56], after maximum tolerated dose has been reached [day 80], and the end of the treatment cycle [day 97]) and once following the 2-week washout period after the second treatment arm (day 112). The questionnaires will be administered by the primary researcher.

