#### Experimental phase

This phase of the study will take 16 weeks to complete. To minimise the risk of adverse events and variation in the maximum tolerated dose of CBM oil, each participant will receive one dose on the first and second days (2 pm) and two doses (9 am and 2 pm) for the reminder of both treatment cycles. A registered nurse will administer the dose along with a small meal (e.g., morning and afternoon tea), and the rate of titration will be monitored by the pharmacist to ensure it is appropriate for each individual. The participant will gradually receive an increased dose (titration) of the medication over several weeks, as shown in Table 1. During these weeks, the participant along with the care staff will record the presence of, and any change in, any potential adverse events that may be associated with the medication after the first dose, each afternoon when the dose is increased, and again on the final day of medication. If an adverse event is noted, the participant will revert to their previous best tolerated dose using the adverse events and safety protocol listed below.

**Table 1 Tab1:** Titration administration, including dose and number of sprays

Day(s)	Week	Dose administered (daily)		Number of spray(s) per dose	Adverse events recorded (time)
		9 am	2 pm		
**1**, 2	1	–	**2.5 m**g	1	3 pm
**3**, 4	1	2.5	2.5	1	
**5**, 6	1	2.5	**5**	1–2	3 pm
**7**, 8	1	5	5	2	
**9**, 10	2	5	**10**	2–4	3 pm
**11**, 12	2	10	10	4	
**13**, 14	2	10	**15**	4–6	3 pm
**15**, 16	2/3	15	15	6	
**17**, 18	3	15	**20**	6–8	3 pm
**19**, 20	3	20	20	8	
**21**, 22	3/4	20	**25**	8–10	3 pm
**23**, 24	4	25	25	10	3 pm

Adverse events will be recorded 1 h after drug administration on days of dose increase (days bolded) and on the last day of the treatment period

An upper limit of 50 mg/day of THC will be permitted in those who do not experience any adverse events from the medication. Once a participant has reached their maximum tolerated dose (or a total of 50 mg/daily of THC), they will continue to receive that dose until the cessation of the 6-week period. The placebo group will follow a similar titration process using the indicated volumes shown in Table 1. They will continue to receive an increase in the volume of medication until they record an onset of an adverse event, at which time they will continue to take that volume of placebo until the end of the 6-week placebo cycle.

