### Adverse events and safety protocol

An adverse events protocol will be put into place to minimise any potential harm or risks of receiving additional medication [14]. This will include participants reporting if they have experienced any adverse events 1 h after the increased dose has been administered (*see* Appendix). If moderate to severe adverse events are recorded (determined as ‘Somewhat worse’ (moderate) or ‘Much worse’ (severe) on the participant’s adverse event record) and these events have not ameliorated by the time for the next dose, the participant will receive the previous best tolerated dose. If the effects of the adverse event(s) have disappeared or become milder and do not interfere with the participant’s daily functioning or well-being, the registered nurse may increase the dose at the indicated rate. Recurrence of adverse events after two attempts to increase the dose will result in the participants remaining at their previous best tolerated dose for the remainder of the intervention period. A participant who experiences an adverse event will stay on the previous dose for another 2 days before the next dose is increased. At the beginning of the titration phase, a staff member at the aged-care facility will be vigilant in monitoring any acute adverse events such as dizziness, discoordination with a danger of falls and injury, and extreme fatigue. Any adverse events recorded will be reported to a facility line manager and will then be communicated to staff during shift changes.

Additional safety monitoring will be completed by a research nurse who will meet with each participant to discuss their adverse event records and measure their heart rate and blood pressure twice per week. In addition, the participant’s weight and non-invasive body composition measures such as lean body mass, bone mass, body fat percentage, and fat mass will be measured once per week using a portable scale. In addition, a nurse-led review will be completed 2 days into the washout periods to monitor the participant’s withdrawal symptoms once no more medication is being administered.

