### Data analysis

#### Quantitative

The results of questionnaires completed on behalf of the aged-care staff, participants and family members will be analysed using IBM SPSS Statistics version 25 software (IBM, Armonk, NY, USA). The responses from the aged-care staff will be the main responses considered for analysis. Where available, participants and family responses will be included for secondary analysis. To examine group differences, the participants will be categorised according to their treatment cycle group allocation (group A or group B). Descriptive statistics will be derived. Each variable will be tested for normality. For those variables that meet the normality assumption, two-sided paired and/or independent *t* tests will be used to examine group differences within and between groups. If the normality assumption is violated, then non-parametric tests such as the Wilcoxon signed-rank test will be used. Within-subject differences of the four measurements between the first and second washout periods will be tested using paired *t* tests to ensure that the washout phase is long enough to rule out any carryover effects [51, 52]. All data collection points will be examined using general linear mixed modelling techniques to see if any changes in behaviour, QOL or pain have occurred over the duration of both treatment cycles. The covariates of weight, average dose of medication, and baseline measures will be controlled for in each model, and any interactions will be tested and reported. The proportion of adverse events during the CBM and placebo phases will be tested and reported for each individual. NPI-NH is the primary outcome measure for this study. All other measures (CMAI, QOL-AD, and Abbey Pain Scale) have been included for secondary analysis. The CMAI will be analysed using the reliability change methodology compared with the NPI-NH to allow small changes to be reported [53]. The α-value will be set at 0.05. In the instance where a participant withdraws halfway through a treatment cycle, the information collected prior to withdrawal will be retained in the study because their personal information will have been de-identified. The data management of the information collected will follow standard university procedures, be stored in a locked cabinet for a period of 15 years, be stored on a password-protected computer, and be backed up regularly in a secure format.

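### The day 24 and day 80 visits are labelled as following the maximum tolerated dose, but the titration and hold rules do not guarantee this, and the cycle 2 end visit is misdated by one day

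*Protocol article*

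**What the plan says.** The Data collection section sets seven questionnaire occasions. The middle one in each cycle falls "after maximum tolerated dose has been reached [day 24" and, in cycle 2, "after maximum tolerated dose has been reached [day 80". The cycle ends are day 42 and, for cycle 2, "the end of the treatment cycle [day 97". Cycle 2 starts on day 56, and the last visit, after the second washout, is on day 112.

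Table 1 (Experimental phase) has twelve two-day rows. The last, 25 mg in the morning and 25 mg in the afternoon, covers days 23 and 24. After that the dose is held constant: "Once a participant has reached their maximum tolerated dose (or a total of 50 mg/daily of THC", the participant stays on it to the end of the six weeks. The same section adds "An upper limit of 50 mg/day of THC will be permitted in those who do not experience any adverse events from the medication". It fixes the placebo volume when a first adverse event is recorded.

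The Adverse events and safety protocol section allows delays: "A participant who experiences an adverse event will stay on the previous dose for another 2 days before the next dose is increased". It also has a stopping rule for escalation: "Recurrence of adverse events after two attempts to increase the dose will result in the participants remaining at their previous best tolerated dose".

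For analysis, the Quantitative section says "All data collection points will be examined using general linear mixed modelling techniques". It names NPI-NH as the primary measure but does not name a primary visit.

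**The concern.** The label treats day 24/80 as an observation at each participant's settled dose. Table 1 leaves no room for this: its top row starts the day before the visit, and a single 2-day hold moves that row past it. The visit can then combine participants who settled weeks earlier, participants on the second day of the top step, and participants still escalating.

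The mix may also differ by treatment. Read literally, the Experimental phase section settles a placebo volume at the first adverse event, while the safety section describes holds and two attempts. Delayed escalation would then arise mainly in CBM cycles.

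The visit enters the mixed model with the others and no visit is named as primary. Day 24/80 scores could therefore be reported as response at the maximum tolerated dose, or weigh on the main CBM-versus-placebo comparison, without the dosing rules supporting that reading.

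**Working it through.** **1. The plan's own sample size.** Inputs from Participants and setting: difference 6, SD of the difference 13, two-sided 5%, 80% power. The normal approximation is (1.960 + 0.842)² × (13/6)² = 36.8. With the noncentral t and N − 2 degrees of freedom, power is 80.1% at N = 39 and 81.2% at N = 40, the even total for two sequences. 40/0.80 = 50. The stated figures reproduce, and 81% is the reference power below.

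**2. Slack in the titration.** Row k of Table 1 starts on day 2k − 1, so row 12 starts on day 23. With h holds of 2 days each and escalation to row 12, the top step starts on day 23 + 2h. Days on it up to day 42 are 42 − (23 + 2h) + 1 = 20 − 2h.

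| Holds | Top step starts | Position on day 24 | Days at top step by day 42 |
|---|---|---|---|
| 0 | 23 | 50 mg/day, second day | 20 |
| 1 | 25 | 45 mg/day (90%) | 18 |
| 2 | 27 | 40 mg/day (80%) | 16 |
| 4 | 31 | 30 mg/day (60%) | 12 |

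Ten holds would be needed before the top step started after day 42 (23 + 20 = 43).

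If the 50 mg/day limit is read as closed to anyone with an adverse event, the last available row is 45 mg/day. It starts on day 23 after one hold and on day 25 after two, so the slack is then one hold rather than none.

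**3. With no adverse event at all.** Table 1 gives 35, 40, 40, 45, 45, 50 and 50 mg on days 18 to 24. The sum is 305 and the mean 305/7 = 43.6 mg, or 87% of the top step. This matters if a rating looks back about a week, as the weekly frequency anchors of the CMAI suggest. The look-back for NPI-NH is not stated, so this is an assumption there.

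**4. Share still titrating on day 24.** The documents give no event rate, so a probability per step is assumed. Rule simulated: an event costs a 2-day hold and a retry, and a second failure at the same step fixes the dose. There were 40,000 simulated participants per cell; exact enumeration agrees within one percentage point.

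| Assumed rate per step | Events possible at all 11 increases | Only at increases whose row shows a 3 pm record |
|---|---|---|
| 1% | 10% | 6% |
| 2% | 20% | 11% |
| 5% | 41% | 26% |
| 10% | 60% | 42% |
| 20% | 62% | 57% |
| 30% | 44% | 54% |

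At high rates the share levels off or falls, because more participants are fixed early and so are at their final dose by day 24.

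**5. Consequence at day 24.** Assume effect proportional to dose, full effect 6, SD 13 and N = 40. If a share q is at dose fraction r, the effect is 6 × (1 − q + q × r).

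| q | r | Effect | Power at day 24 |
|---|---|---|---|
| 10% | 90% | 5.94 | 80% |
| 25% | 80% | 5.70 | 77% |
| 50% | 80% | 5.40 | 73% |
| 50% | 60% | 4.80 | 62% |

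The last row needs half the participants to have had four holds each.

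**6. Visit dates.** Cycle 1 offsets are 0, 24 and 42. In cycle 2, 80 − 56 = 24 agrees, but 97 − 56 = 41 does not. Both 56 + 42 and 112 − 14 give 98.

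**The case against.** A fair defence makes five points.

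- **The visit may be tied to an event.** The bracketed day could be nominal, for an undelayed titration. The wording allows this, but the visit day would then vary by participant and perhaps by treatment. The text needs to say which is meant.
- **Not every adverse event causes a hold.** The safety section ties reversion to moderate or severe events that have not eased by the next dose, and otherwise lets the nurse proceed. This stands and favours the lower part of the range in step 4.
- **Different doses are intended.** Titration is individual, so doses differ between participants on day 42 too. This stands. What is particular to day 24 is the mix of titrating and settled participants under a label that says all are settled.
- **The model can absorb it.** The plan says interactions will be tested, and it does not say that visits will be averaged. This stands, and the exact model form may be left to the analysis plan. It does not correct the label or settle which visit carries the primary contrast.
- **The end-of-cycle visit is sound.** It is collected in both cycles and is robust to several holds. This stands and is why the remedy is cheap.

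A reader might go further and infer that most participants will still be titrating on day 24, or that the trial loses a large part of its power. The documents support neither. The chance of having had any hold is not the share still titrating, because the two-attempt rule leaves some held participants already at their final dose. A large power loss would need a much reduced day 24 effect averaged with the end-of-cycle effect, and the plan states neither.

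**Conclusion.** The concern holds in limited form. The day 24/80 label contradicts Table 1 and the hold rule: at best the participant is on the second day of the top step, and one or two holds, depending on how the 50 mg/day limit is read, put the final dose after the visit. The cycle 2 end visit is misdated by one day, which is certain but has little statistical weight.

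The number of participants affected cannot be fixed from the documents; the 6% to 62% range rests on assumed rates. The power range at day 24 rests on a dose-proportional effect and an unchanged SD, and only its extreme corner shows a substantial loss. The main consequence is therefore interpretive: day 24/80 should not be read as full-dose response. Its meaning may also differ between CBM and placebo until the two accounts of what follows a first adverse event are reconciled. Which of those rules should apply is not judged here.

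**What to change.** - In Data collection, call day 24 and day 80 mid-cycle visits and do not report them as response at the maximum tolerated dose.
- Correct day 97 to day 98.
- Name the end-of-cycle visits (days 42 and 98) as the primary CBM-versus-placebo contrast on NPI-NH.
- Keep mid-cycle scores in the mixed model with a treatment-by-visit term, so that a smaller mid-cycle effect does not pull on the primary contrast.
- Describe, by treatment, the dose taken and the days on it at each visit.
- Reconcile the Experimental phase and safety sections on what follows a first adverse event, for CBM and for placebo, and on who may reach the upper limit.

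The cost is wording in the visit schedule and the analysis section. No visit is added, and the statistical changes alter no dosing rule. The downside is that the mid-cycle score no longer counts as a full-dose observation.

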### Adverse events and safety protocol

An adverse events protocol will be put into place to minimise any potential harm or risks of receiving additional medication [14]. This will include participants reporting if they have experienced any adverse events 1 h after the increased dose has been administered (*see* Appendix). If moderate to severe adverse events are recorded (determined as ‘Somewhat worse’ (moderate) or ‘Much worse’ (severe) on the participant’s adverse event record) and these events have not ameliorated by the time for the next dose, the participant will receive the previous best tolerated dose. If the effects of the adverse event(s) have disappeared or become milder and do not interfere with the participant’s daily functioning or well-being, the registered nurse may increase the dose at the indicated rate. Recurrence of adverse events after two attempts to increase the dose will result in the participants remaining at their previous best tolerated dose for the remainder of the intervention period. A participant who experiences an adverse event will stay on the previous dose for another 2 days before the next dose is increased. At the beginning of the titration phase, a staff member at the aged-care facility will be vigilant in monitoring any acute adverse events such as dizziness, discoordination with a danger of falls and injury, and extreme fatigue. Any adverse events recorded will be reported to a facility line manager and will then be communicated to staff during shift changes.

Additional safety monitoring will be completed by a research nurse who will meet with each participant to discuss their adverse event records and measure their heart rate and blood pressure twice per week. In addition, the participant’s weight and non-invasive body composition measures such as lean body mass, bone mass, body fat percentage, and fat mass will be measured once per week using a portable scale. In addition, a nurse-led review will be completed 2 days into the washout periods to monitor the participant’s withdrawal symptoms once no more medication is being administered.

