Studies assessing the safety and efficiency of CBMs have shown many benefits among other neurodegenerative diseases, such as Parkinson’s disease [33, 34], epilepsy, post-traumatic stress disorder [18, 35], anxiety [12], and spasticity due to multiple sclerosis [36], with the use of CBM reducing benzodiazepine prescriptions by 45% [37]. However, only a handful of studies have investigated the use of CBM in patients with dementia [13, 14, 23]. Recently, an observational study monitored the use of a CBM medication over a 2-month period among ten females with severe dementia and found a 40% reduction in behavioural problems and 50% reduction in rigidity [38].

The pharmacodynamics and pharmacokinetics of THC (weeks 1–6, 0.75 mg; weeks 7–12, 1.5 mg) administered to ten participants with dementia was safe and well tolerated [14]. Administration of THC 2.5 mg in 11 patients with dementia demonstrated positive effects on mental state; dementia severity; and behavioural symptoms such as delusions, irritability, sleep and caregiver distress [23]. Studies reporting the use of dronabinol (2.5 mg daily) found improvements in anorexia and body weight, as well as less disturbed behaviours [16] such as agitation and motor behaviours, with no adverse effects observed [39]. Retrospective observations of dronabinol administration among 40 hospitalised patients indicated improvements in agitation and aggression, sleep duration, and meal consumption [13]. Two independent case studies monitoring the effects of nabilone (maximum dose 0.5 mg twice daily for 6 weeks) among elders with dementia found improvements in severe agitation and aggression [40], psychomotor activity, and smiling, as well as positive experiences among family members [41]. No changes in the number of falls or in balance (with eyes open) were reported among 18 participants administered 1.5 mg of oral THC twice daily [42], with recommendations suggesting higher doses (THC 1.5 mg three times daily), and longer study durations (great than 3 weeks) are needed to understand the true effects on behavioural symptoms, including QOL and activities of daily living [43]. Therefore, further research in this area is needed because many beneficial outcomes have been reported, although dosing, samples size, patient cohort (2–50 participants) and outcomes have varied in what are generally small studies with poor experimental designs.

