## Appendix

### Adverse events associated with THC and CBD

Adverse events will most likely occur within 1 h of administration of the medication but will often resolve within 48 h of treatment. Participants will report their adverse events to make sure the titration is appropriate for them.

Compared with how you normally feel, have you experienced a change in any of the symptoms described below in the last hour? Tick the most appropriate box below.

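### Falls and injuries are a named danger, but the adverse event form has no item for them and is not scheduled on days 25 to 41, when the dose is held at its highest

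*Protocol article*

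**What the plan says.** All references are to the protocol article.

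- **Aims.** Whether the oil is safe is part of the primary aim.
- **Adverse events and safety protocol.** The text names the danger: "At the beginning of the titration phase, a staff member at the aged-care facility will be vigilant in monitoring any acute adverse events", with the examples "dizziness, discoordination with a danger of falls and injury, and extreme fatigue". Recorded events go to a facility line manager. A research nurse meets each participant to discuss the adverse event records and takes heart rate and blood pressure twice per week. A nurse-led review follows 2 days into each washout.
- **Experimental phase, text.** Recording is shared: "the participant along with the care staff will record the presence of, and any change in, any potential adverse events". It takes place after the first dose, on the afternoons of dose increases, and on the final day.
- **Experimental phase, note to Table 1.** "Adverse events will be recorded 1 h after drug administration on days of dose increase (days bolded) and on the last day of the treatment".
- **Experimental phase, dose.** "An upper limit of 50 mg/day of THC will be permitted in those who do not experience any adverse events from the medication". Once participants reach their maximum, "they will continue to receive that dose until the cessation of the 6-week period".
- **Appendix.** The form asks: "have you experienced a change in any of the symptoms described below in the last hour". Its 16 items include dizziness, drowsiness/fatigue and lack of coordination. None is a fall or an injury. Its footnote confines use to titration and the last dose of each arm.
- **Data analysis, Quantitative.** The proportion of adverse events in the CBM and placebo phases will be tested and reported.

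**The concern.** The safety comparison can use only what the data collection delivers. Here the form is printed in full, with its recall window and schedule, so these are fixed choices and not details left to another document. Followed as written, they suit short-lived symptoms in the hour after a dose increase. They do not suit falls, which can happen at any hour and on any day.

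Participants are 65 or older and not bedridden (Participants and setting), so falls are a plausible harm. The Background's own evidence on falls comes from a much lower exposure: "No changes in the number of falls or in balance (with eyes open) were reported among 18 participants administered 1.5 mg of oral THC twice". At two doses a day, that is 3 mg/day. The permitted ceiling here is 50 mg/day, about 17 times that (50 / 3 = 16.7). The earlier result therefore cannot stand in for a count in this trial. Without such a count, a conclusion that the oil is safe would not cover a danger that the protocol itself names.

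**Working it through.** **Inputs.** Daily THC is the 9 am plus the 2 pm dose in Table 1. The cycle lasts 42 days. The calculation is for a participant who completes titration and then holds the final dose.

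**Check of the plan's figure.** The last row of Table 1 is 25 + 25 = 50 mg/day, and 10 sprays × 2.5 mg × 2 doses = 50 mg/day. Both agree with the stated ceiling.

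**Cumulative THC in one cycle**

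| Days | Calculation | THC | Share |
|---|---|---|---|
| 1–24 | 2 × (2.5 + 5 + 7.5 + 10 + 15 + 20 + 25 + 30 + 35 + 40 + 45 + 50) = 2 × 285 | 570 mg | 38.8% |
| 25–42 | 18 × 50 | 900 mg | 61.2% |
| Whole cycle | 570 + 900 | 1,470 mg | 100% |
| 25–41 (no form scheduled) | 17 × 50 | 850 mg | 850 / 1,470 = 57.8% |

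Days 25–41 are 17 of 42 days, or 40.5% of the cycle.

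**Scheduled use of the form**

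- Table 1 marks a 3 pm recording in seven rows, starting on days 1, 5, 9, 13, 17, 21 and 23. With the last day this gives 8 occasions.
- If every bolded day counts as a dose-increase day, there are 12 + 1 = 13 occasions.
- Each occasion looks back one hour. The cycle has 42 × 24 = 1,008 hours. Coverage is 8 / 1,008 = 0.8% to 13 / 1,008 = 1.3% of the cycle.

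**Route of a fall into the analysis.** Take a fall on day 30. No form is due that day. The next scheduled form is on day 42, asks about the last hour and has no fall item. The nurse discusses the adverse event records, but none is scheduled on days 25–41. The fall is counted only if someone reports it unprompted.

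**Contacts available to close the gap.** The Abstract (Methods/design) has heart rate and blood pressure taken weekly; Adverse events and safety protocol has them twice per week. Over 17 days that is about 2.4 contacts (17 / 7) or 4.9 contacts (2 × 17 / 7).

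**The case against.** The strongest case against is that the sentence on staff vigilance adds to the surveillance and does not define it. Care staff record together with the participant at each scheduled rise, up to the step to 50 mg/day, and again on the last day. The symptoms that commonly precede a fall are form items. Nurse contacts, line-manager reporting and washout reviews are not limited to titration. A fall reported as an adverse event would enter the comparison by phase. A condensed article may also leave fall definitions and incident reporting to the full protocol.

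Most of this stands, and it rules out a stronger reading. A reader might infer from "At the beginning of the titration phase, a staff member at the aged-care facility will be vigilant in monitoring any acute adverse events" that observation lapses as the dose rises and that falls go uncounted over nearly all of the exposure. The document does not support that, because scheduled recording follows the dose upward to day 23. Nor can the missed share be taken from the dose given while staff are vigilant. That share is 40 / 1,470 = 2.7% if the beginning means days 1–7 and 170 / 1,470 = 11.6% if it means days 1–14. The text does not define the word, and neither figure measures missed falls.

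What the objection does not meet is the printed form. Its items, recall window and schedule are stated, and none of the other contacts is said to ask about falls.

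**Conclusion.** The point holds in a limited form. Falls and injuries, which the protocol names as a danger, have no form item and no stated systematic count by phase. The gap is widest on days 25–41, which carry 57.8% of the cycle's THC for a participant who completes Table 1. It does not extend to dizziness, fatigue or lack of coordination during titration, and it does not show that every fall would be missed.

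The 57.8% assumes titration on the printed calendar. A participant who settles early on a lower dose may have no scheduled form from an earlier day. One whose increases are delayed by adverse events may have forms later than day 23. The figure is a share of exposure without a scheduled form, not a share of falls lost. The documents give no fall rate, so the number of falls at stake cannot be calculated. The sample size is unaffected.

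**What to change.** 1. Add a dated fall and injury item to the adverse event record, with recall since the last contact. Collect it at the research nurse contacts already planned through both cycles and at the washout reviews. Supplement it from facility incident records, assuming these exist; the article does not mention them.
2. In Data analysis, Quantitative, add a within-person comparison between the CBM and placebo cycles of the number of falls and the proportion of participants who fall. The dates allow each fall to be assigned to a cycle, to titration or maintained dose, or to washout.
3. Reconcile the nurse visit frequency between the Abstract (weekly) and Adverse events and safety protocol (twice per week), since the new item depends on it.

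The cost is a small amount of extra data entry and one safety table. Dosing and sample size do not change.
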